**Fig. 1 Fig1:**
[figure not shown]
CONSORT 2010 flow diagram

### Setting

The study will be carried out at an outpatient clinic at Copenhagen University Hospital, Amager and Hvidovre, Denmark. The outpatient clinic is specialized in providing interdisciplinary antenatal care for psychosocially vulnerable pregnant women. In Denmark, there is free and equal access to most healthcare services including hospitals, general practitioners, and practicing specialists. The International Classification of Diseases, Tenth Revision (ICD-10) is used for the classification of diseases. The Copenhagen University Hospital, Amager and Hvidovre, is located in the greater Copenhagen area and is the country’s largest birthplace with 7000 annual births. Every year, about 800 pregnant women are referred to the outpatient clinic by their general practitioner with the first consultation being around 18 weeks’ gestation. Reasons for referral are past or present mental disorders, substance abuse, or other psychosocial vulnerabilities such as domestic violence or a history of sexual abuse. About 66% of all referrals are substantiated by a psychiatric diagnosis.

### Recruitment and consent

Pregnant women referred to the outpatient clinic are recruited at their first or second consultation with a midwife. The first consultation is on average approximately 18 weeks’ gestation and the second approximately 24 weeks’ gestation. In order to determine eligibility, the midwife will use the information from the patient record regarding reasons for a referral to the outpatient clinic. The information includes past or present psychiatric diagnoses, and past or present substance abuse. The information is registered in an Excel sheet along with name and contact information and passed on to the responsible researcher. The midwife will provide verbal information about the study and email written information to eligible women, who express an interest in participating in the study. An online zoom interview is then scheduled with the responsible researcher. The women will be encouraged to find a time and a place where the interview can take place undisturbed, and information is provided about the possibility of having a partner or other person present. The online format provides the women with an opportunity to participate in the interview in their own homes as they may feel particularly vulnerable during the corona pandemic. The corona pandemic, coupled with our experience working with this population, led to offering this option. If an online interview is not possible, the interview will be conducted at the outpatient clinic. The interview will contain information about the study such as study criteria, procedures, randomization, intervention, and motivation for study participation. Women who consent to study participation will be asked to sign the consent form within 1 week from the interview. The women can choose to either return a signed consent form by email or sign the consent form at the outpatient clinic, who will then return it to the responsible researcher.

### Inclusion and exclusion criteria

The aim of the study is to address prenatal mental care in psychosocially vulnerable women with no particular attention to any specific psychiatric diagnosis or other psychosocial vulnerability. However, there are some cases where MBSR is not suited, which is specified in the exclusion criteria.

The following are the inclusion criteria:
Estimated due date no sooner than 3 months from the start of the intervention. The adapted MBSR program includes nine weekly sessions, and these criteria were included in order for the women to be able to complete the intervention.Eighteen + years of age.Speak and write Danish.Available for group intervention scheduled sessions. Being unavailable for two or more sessions is a reason for exclusion from study participation.Written informed consent to study criteria.

The following are the exclusion criteria:
Concurrent substance abusePsychotic disorders and post-traumatic stress disorderSuicidality

### Criteria for discontinuing allocated interventions

The criteria for discontinuation of study participation are (1) if requested by the participant, and (2) if the participant is absent from the prenatal MBSR class for two consecutive sessions and does not respond to email or phone calls.

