### Study aim and objectives

The primary aim of the study is to determine the feasibility and acceptability of the prenatal MBSR program delivered to psychosocially vulnerable pregnant women in a hospital-based setting. The objectives are to examine the following: (1) acceptance of trial participation; (2) acceptance of allocated interventions; (3) risk of bias: loss to follow-up in the study arms, acceptance and compliance with the intervention, i.e., attending ≥ 5 sessions; and (4) the extent of missing data leading to missing outcomes. The secondary aim is to explore the potential efficacy of the prenatal MBSR program on self-reported measures of stress, well-being, anxiety, depression, reflective functioning, mindfulness, and self-compassion. The outcomes of the feasibility study will inform the design of a fully powered RCT.

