## Methods/design

### Design

The protocol is for a randomized, single-center feasibility trial comparing the prenatal MBSR program as an add-on to usual care with usual care alone. Participants will be randomized in a 1:1 ratio to an intervention or waitlist control group. A completed SPIRIT checklist is available in Additional Files and the study flow is outlined in Fig. 1. Self-report measures will be collected at three time points: (1) at baseline prior to randomization, (2) immediately after completion of the prenatal MBSR program, and (3) 3 months post-completion. Participants in the waitlist control group will be offered participation in a MBSR program after completion of the study.

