### Data analyses

Statistical analyses will be performed using SPSS for Windows (version 27; IBM Corp, Armonk, NY). Skewness, kurtosis, and visual inspection of normal Q-Q plots will be used to inspect normality. Descriptive statistics will be presented as mean and SDs or median and interquartile range (IQR) depending on the distribution of the continuous variables or as frequencies for categorical variables.

Recruitment, participation, and retention rates will be reported and presented in a CONSORT flow diagram [40]. Data collected on numbers of eligible participants recruited, numbers randomized, adherence to, and compliance with the intervention, as well as dropouts lost to follow-up, will be presented as percentages and used to inform the development of a full-scale RCT.

Acceptability of the intervention will be assessed by dropout rates, by computing the mean number of completed sessions, and time spent on at-home practices in the prenatal MBSR group. Participation in ≥ 5 sessions will be considered compliant with the program. A loss to 12-week follow-up analysis will be conducted for age, education, employment, history of a mental disorder, participation in < 5 sessions of the intervention, and pre-scores on the PSS-10 by means of t-test and chi-squared test (χ^2^). A loss to intervention analysis will be conducted for participants attending < 5 sessions of the intervention applying a similar approach.

Analyses of a possible effect of the intervention will be performed based on the intention-to-treat principle, meaning that all participants will be included in the analysis irrespective of their compliance with the intervention protocol. Lastly, an additional per-protocol analysis will be conducted. Since the study is not powered by formal hypothesis testing, only effect estimates and 95% CIs will be presented in accordance with the CONSORT criteria for reporting of feasibility or pilot studies [40].

Independent t-tests (or the non-parametric equivalent Mann-Whitney U) will be conducted to compare the pre- and post-questionnaire scores of the intervention and control groups. In case of skewed distributions in baseline variables, e.g., age and history of mental disorders, logistic regression analyses will be performed.

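### The discontinuation criteria do not settle whether the intervention or study participation ends; read literally, one criterion can remove women from the MBSR arm only

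*Protocol article*

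**What the plan says.** The section is headed "Criteria for discontinuing allocated interventions", but its only sentence begins: "The criteria for discontinuation of study participation are (1) if requested by the participant, and (2) if the participant is absent". The second criterion applies to a woman who is "absent from the prenatal MBSR class for two consecutive sessions and does not respond to email or phone calls".

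Four other places bear on this:

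- **Design**, on the control arm: "Participants in the waitlist control group will be offered participation in a MBSR program after completion of the study".
- **Data analyses**, on the effect analysis under intention to treat: "all participants will be included in the analysis irrespective of their compliance with the intervention protocol". A separate analysis set is also planned: "Lastly, an additional per-protocol analysis will be conducted".
- **Study aim and objectives** lists among the feasibility objectives: "risk of bias: loss to follow-up in the study arms".
- **Data analyses**, on who is lost: "A loss to 12-week follow-up analysis will be conducted for age, education, employment, history of a mental disorder". The same list goes on to attendance at fewer than 5 sessions and the baseline PSS-10 score.

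No section says whether questionnaires continue or stop once a woman is discontinued, or whether data already collected are kept.

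**The concern.** Stopping classes and leaving the study are different events. After the first, a woman's outcomes can still be collected; after the second, they normally are not. The heading points to the first and the operative sentence to the second.

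This matters because the second criterion is tied to class attendance, which exists in one arm only. A waitlist woman who stops answering meets neither criterion and stays in follow-up, with questionnaire reminders. An MBSR woman who stops answering and misses two classes in a row is, on the literal text, out of the study.

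Two things are at stake. First, the comparison of arms could lose its least engaged women on one side only, although the stated principle is to include everyone regardless of compliance. Second, retention by arm is one of the quantities this trial exists to measure for the full RCT. If the rule itself causes part of the loss, the retention figure passed on is not the one the full trial needs.

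**Working it through.** The plan has no figure of its own to reproduce on this point. It gives no expected dropout, no SD and no attendance rate, and it states that it is not powered for hypothesis testing. The check is therefore a comparison of passages, followed by an illustration on assumed inputs.

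**1. Passages side by side**

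| Question | Discontinuation section | Elsewhere in the article |
|---|---|---|
| What ends? | Heading: the intervention. Text: study participation. | Not stated |
| Who can meet criterion 1 (request)? | Both arms | – |
| Who can meet criterion 2 (missed classes and no reply)? | MBSR arm only | Design: MBSR is offered to the waitlist only after the study |
| Does non-attendance affect inclusion? | Yes, on the literal text | Data analyses: no |
| Are poor attenders still followed? | No, on the literal text, if they also do not reply | Presumed: fewer than 5 sessions is examined as a correlate of loss at 12 weeks |

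Under the literal text, the last row becomes partly circular: low attendance is then one cause of the loss it is meant to help explain. The factor also has no meaning for waitlist women.

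**2. Inputs for the illustration**

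- From the documents: 60 women randomized 1:1, so 30 per arm.
- Assumed: a fraction *f* of MBSR women meeting criterion 2, from 10% to 30%.
- Assumed: a difference *d* in outcome between women removed and women retained, from 0.3 to 0.8 SD.

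**3. Shift in the MBSR mean if the removed women would all have responded**

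Shift = *f* × *d*.

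- Low: 0.10 × 0.3 = 0.03 SD
- Middle: 0.20 × 0.5 = 0.10 SD
- High: 0.30 × 0.8 = 0.24 SD

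**4. Allowing for women who would not have responded anyway**

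Take the middle case: 0.20 × 30 = 6 women meet the criterion and 24 remain. Assume that a share *q* of the six would have returned a questionnaire.

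Shift caused by the rule = 6*q* / (24 + 6*q*) × 0.5. Retention lost to the rule = 6*q* / 30.

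- *q* = 25%: 1.5 / 25.5 × 0.5 = 0.03 SD, and 1.5 / 30 = 5 percentage points
- *q* = 50%: 3 / 27 × 0.5 = 0.06 SD, and 3 / 30 = 10 percentage points
- *q* = 100%: 6 / 30 × 0.5 = 0.10 SD, and 6 / 30 = 20 percentage points

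**5. Precision, for scale**

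The half-width of the 95% CI for a difference in means, in SD units, is 1.96 × √(1/30 + 1/m), with m MBSR women retained.

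- m = 30: 0.51
- m = 27: 0.52
- m = 24: 0.54
- m = 21: 0.56

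The loss of precision is small. Any harm lies in selective loss and in the retention estimate.

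**The case against.** The strongest reply is that the rest of the article points away from the literal reading. The heading speaks of the intervention. The effect analysis includes everyone regardless of compliance. Questionnaire reminders exempt nobody. Women who cancel two consecutive sessions are to be phoned and their midwife informed, so as to prevent dropout. On this view the sentence is loosely worded and follow-up would continue. That may well be the intention, and it limits what can be claimed. It does not remove the contradiction, because staff applying the sentence as written would end participation.

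A reader might infer four stronger things that the documents do not support:

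- **That the whole rule is one-sided, breaks intention to treat and discards outcomes.** Criterion 1 is open to both arms, and criterion 2 needs non-response as well as absence. No passage says that questionnaires stop or data are dropped. One-sided loss is a risk under the literal text, not an established consequence.
- **That the effect will be biased in favour of MBSR.** This requires women who stop attending to have worse scores, and nothing in the article says so.
- **That the planned reporting cannot reveal the problem.** Loss in the study arms is an objective, and retention is to be shown in a CONSORT flow diagram, so loss by arm will be visible. Without recorded reasons, the diagram would not separate loss due to the rule from ordinary loss.
- **That the compliance definition contradicts the rule.** A woman could attend sessions 1–5, miss 6 and 7 without replying, and be both compliant and discontinued. That is awkward but consistent: compliance is a session count, and a compliant woman can later be lost.

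**Conclusion.** The point holds in a limited form. The discontinuation section contradicts itself on what ends. On the literal reading, criterion 2 can remove women from the study in the MBSR arm only. That conflicts with the commitment to analyse everyone irrespective of compliance, and with the use of low attendance as a factor in the loss analysis. It may also make part of the loss to follow-up an artefact of the rule.

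The size is unknown. The range of about 0.03–0.24 SD is a ceiling for the assumed inputs, and it falls to the extent that non-responding women would have been missing anyway. Against a CI half-width of about 0.51 SD with 30 per arm, even the upper end is well inside the uncertainty of the effect estimate. The more direct consequence is for the retention figure, which is a primary concern of a feasibility trial: 5 to 20 percentage points in the MBSR arm in the middle case, as the assumed share of would-be responders runs from 25% to 100%.

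**What to change.** 1. Reconcile the heading and text of the discontinuation section with each other and with the intention-to-treat statement in Data analyses. How class attendance and stopping of classes are managed stays with the sponsor; no rule on that is proposed here.
2. State that the post-programme and 3-month questionnaires are sent to every randomized woman in both arms unless she herself withdraws from data collection.
3. Report loss at each of the two time points by arm, with reasons, so that discontinuation under criterion 2 can be told apart from other loss.
4. Use the factor for fewer than 5 sessions in the MBSR arm only.

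The cost is a few sentences and a reason-for-loss field. The REDCap questionnaires and reminders already exist, so no extra visits or participants are needed. The study started in mid-January 2021, so the clarification should also reach the staff who send the questionnaires.

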### The intervention

#### The prenatal MBSR program

When adapting MBSR to high-risk pregnancies, the essential program elements characterizing MBSR were maintained [16] and integrated with the particular context and specific needs of pregnant women. The process of adapting MBSR is described in detail in the following.

The adaptations draw upon both empirical data as well as existing research and theory. The process of adapting the MBSR program was led by a psychiatrist, with extensive clinical and MBSR teaching experience, in collaboration with psychologists and researchers with relevant clinical and/or MBSR teaching experience.

In terms of empirical data, all staff at the outpatient clinic initially participated in a standard MBSR program. The purpose was for the staff to get a sense of what mindfulness training involves, by experiencing it for themselves, and, further, to generate knowledge that could inform the organization of an MBSR course for psychosocially vulnerable pregnant women. Thus, two focus group interviews with the staff were conducted after finalizing the 8-week MBSR course. The interview questions assessed the potential barriers for program attendance, the structure of the program, how to provide the best support to ensure attendance, and criteria for success.

The prenatal MBSR program has been pretested in five groups of pregnant women referred to the outpatient clinic. There was a maximum of 15 participants in each group. A psychiatrist and a psychologist with extensive clinical experience and MBSR teaching experience taught the groups. A midwife or a psychologist, from the outpatient clinic, participated in each of the groups. Pre- and post-self-report measures were collected. Attendance and dropout rates were systematically registered. Subsequent individual interviews with the participants and participating staff resulted in some adjustments to the program. In sum, the developmental process resulted in the following adaptations to the standard MBSR program: The first adaptation is that the prenatal MBSR program consists of nine 2-h sessions and no full-day  session. The rationale for including shorter sessions and no full-day sessions is to make the program more adaptable for the clinical context that it is intended for. The second adaption relates to the fact that transition to motherhood is often presented as an exciting and joyful time with naturally developing emotional growth by modern society and the media [24]. The idealistic image may not be a close representation of the actual experience for women with mental health or severe psychosocial problems. Therefore, the program emphasizes a particular focus on the mother-child relationship by drawing attention to the bodily sensations, emotions, and thoughts associated with pregnancy and motherhood as they unfold. The third adaptation includes a yoga program that is suitable for pregnancy. , The fourth includes shortened sitting meditations  and greater alternation, during sessions, between meditation exercises in order to accommodate the bodily changes associated with pregnancy. The fifth adaptation includes a reduced 15-min daily mindfulness practice, with options for longer practice; this is to make it more manageable considering the vulnerabilities and life circumstances of these women. Lastly, the sixth adaptation to the program is that it is delivered in a combination of physical attendance (sessions 1, 4, and 9) and online delivery. Combining physical attendance with online delivery reduces traveling time and ensures attendance. This is while still providing a good starting point for establishing a learning environment and the feeling of being part of a group. Online booster sessions will be offered every 3 months after finalizing the 9-week program and continues throughout the first postnatal year. Mothers are invited to bring their babies to the booster sessions thereby making it an opportunity to practice being mindful with their babies.

#### Instructor qualifications

The prenatal MBSR program will be delivered by two highly trained MBSR teachers from the Danish Center for Mindfulness, Aarhus University. Both have been involved in the process of adapting the MBSR program to the present context and have extensive clinical psychiatric experience.

#### Usual care (TAU)

Standard clinical practice, usual care (TAU), consists of routine pregnancy visits to the outpatient antenatal clinic at Copenhagen University Hospital, Amager and Hvidovre, and to a general practitioner. A multidisciplinary approach involves primarily preventive counseling by midwives and, in some cases, consultations with a physician or social worker throughout the pregnancy and follow-up until the early post-partum period. In some cases, usual care may include consultations with a psychologist, although usually limited to a few sessions, and in more severe cases, referral to psychiatric treatment. All consultations are individual, and the first session is planned in gestational week 18, with an average of six following consultations. Additional consultations are planned if deemed necessary.

### Primary outcome: feasibility of a full-scale RCT

The primary outcome of the study is to access the feasibility of a full-scale RCT, including accessing acceptance of trial participation among psychosocially vulnerable pregnant women. Acceptance of trial participation includes recruitment rate, acceptance of allocated interventions, compliance (i.e., attending ≥ 5 sessions), non-completion, and adverse events.

The recruitment process will be systematically registered in close collaboration between the Danish Center for Mindfulness, Aarhus University, and the outpatient clinic at Copenhagen University Hospital. Project meetings, every other week, will provide an opportunity for continuous evaluation of the recruitment process.

Prenatal MBSR class attendance will be registered at each session, and participants will be asked to notify the teacher in case of non-participation. Participants canceling two consecutive sessions will be contacted by phone, and the responsible midwife will be informed in order to provide support and prevent dropout. Adherence and acceptability of the prenatal MBSR program will be evaluated after the trial is finalized by examining attendance, time spent on home practice, and overall satisfaction with the program. On a daily basis, participants will be asked to register time spent on home practice. Satisfaction with the program will be evaluated at the last session. The prenatal MBSR teacher will register any adverse event ascribed to the prenatal MBSR program and notify the responsible researcher.

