### Blinding

Group affiliation will be concealed for the researcher performing the statistical analyses.

Participants will not be blinded. Keeping participants blind to this type of intervention would not be possible. Part of the study is to understand if this introduces any difficulties (i.e., resentful demoralization) into the study that would need to be addressed before a larger trial.

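### Satisfaction is rated only by women present at session 9, and no described measure asks usual-care women how they reacted to their allocation

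*Protocol article*

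**What the plan says.** Feasibility and acceptability form the primary aim. Under the primary outcome, adherence and acceptability are to be evaluated "by examining attendance, time spent on home practice, and overall satisfaction with the program". Each component has its own collection rule:

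- Attendance: "Prenatal MBSR class attendance will be registered at each session".
- Home practice: "On a daily basis, participants will be asked to register time spent on home practice".
- Satisfaction: "Satisfaction with the program will be evaluated at the last session".

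On format, the intervention section says of the program that "it is delivered in a combination of physical attendance (sessions 1, 4, and 9) and online delivery", so the last session is one of three attended physically.

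The Data analyses section describes acceptability differently: "Acceptability of the intervention will be assessed by dropout rates, by computing the mean number of completed sessions, and time spent on at-home practices". Satisfaction is not in that list.

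On unblinded participants, the Blinding section states: "Part of the study is to understand if this introduces any difficulties (i.e., resentful demoralization) into the study". It adds that such difficulties would have to be dealt with before a larger trial. Acceptance of the allocated interventions is an objective and a component of the primary outcome, and it is not limited to one arm. Both arms complete self-report questionnaires at baseline, after the program and three months later.

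**The concern.** Satisfaction is the only listed acceptability component that records the women's own judgement of the program. Attendance and dropout show that a woman left, not what she thought of it. Collecting the rating only at the last in-person class leaves out those who stopped, whose opinion matters most for adapting the program before a full trial.

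The second issue is a mismatch between a declared purpose and the measures described. The control group is a waitlist whose members know they did not receive the program. If the study is meant to learn whether that knowledge causes difficulties, something has to capture it. If nothing does so directly, the full trial will be designed with that question still largely open.

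**Working it through.** The article gives no figure on either point, so there is nothing to reproduce. The check traces who can supply each piece of information and then illustrates the size with assumed rates.

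**Who can rate satisfaction**

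1. The rating is taken at session 9 of nine weekly sessions, eight weeks after session 1. The due date must be at least 3 months (about 13 weeks) after the start, so for the latest eligible woman session 9 falls about 13 − 8 = 5 weeks before her due date.
2. Compliance means at least five of nine sessions, so a compliant woman can miss session 9.
3. Unavailability for two or more sessions excludes a woman. One who is unavailable for session 9 alone remains eligible.
4. A woman absent for two consecutive sessions who does not respond to contact is discontinued. She would not be there to rate.

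**Illustrative size**

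The only inputs from the article are 60 participants and 1:1 allocation, hence about n = 30 in the MBSR arm. Attendance at session 9 (m), the number satisfied among attenders (s, about 90%) and a 40% satisfaction rate among absentees are assumptions.

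- Reported value: s/m
- Lowest whole-arm value: s/n
- Highest whole-arm value: (s + n − m)/n
- Whole-arm value if 40% of absentees are satisfied: (s + 0.4(n − m))/n

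| m | s | Reported | Lowest | Highest | If 40% of absentees satisfied |
|---|---|---|---|---|---|
| 27 | 24 | 24/27 = 89% | 24/30 = 80% | 27/30 = 90% | 25.2/30 = 84% |
| 21 | 19 | 19/21 = 90% | 19/30 = 63% | 28/30 = 93% | 22.6/30 = 75% |
| 15 | 14 | 14/15 = 93% | 14/30 = 47% | 29/30 = 97% | 20/30 = 67% |

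The upper bound exceeds the reported value in every row, so the direction of error is not fixed by arithmetic alone. It is upward only if absentees are less satisfied than attenders.

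**What bears on resentful demoralization**

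1. The questionnaires cover stress, anxiety, depression, well-being, decentering, reflective functioning, mindfulness and compassion. None asks about reaction to allocation.
2. The primary outcome section details attendance, home practice, satisfaction and adverse events ascribed to the program, all in the MBSR arm. Data analyses contains nothing on reaction to allocation.
3. What remains is indirect: loss to follow-up by arm and control-arm scores. With 30 per arm and the same dropout p in both, the 95% half-width for the difference is 1.96 × √(2p(1 − p)/30). For p = 10%, 20% and 30% (assumed) this gives about 15, 20 and 23 percentage points.
4. The score comparison cannot isolate demoralization either. A between-arm difference combines any benefit of MBSR with any worsening caused by disappointment in controls, and a fall within the control arm could equally reflect illness or advancing pregnancy.

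**The case against.** Much can be said for the plan. Acceptability is broader than satisfaction. Attendance at every session, daily home practice and dropout all count early leavers, and the Data analyses section also compares women attending fewer than five sessions with the rest. A reader might infer that acceptability as a whole is estimated from completers; the article does not support that.

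A reader might also infer that nothing is asked of controls, or that the demoralization question cannot be answered at all. Neither is supported. Controls complete questionnaires at three time points, their retention is examined, and staying or withdrawing after allocation is an ordinary behavioural measure of acceptance. They are also offered a program after the study. These sources give some evidence, though indirect and imprecise.

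Three further inferences go beyond the text. The article does not say who administers the satisfaction rating, so influence from the teachers cannot be asserted. It does not say that the choice of comparator for the full trial depends on demoralization. And although "all staff at the outpatient clinic initially participated in a standard MBSR program", the stated reasons were to experience the training and to inform its organization. Nothing says staff use it in usual care, so contamination of the control arm cannot be inferred.

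Finally, a journal article condenses a fuller protocol, which may contain a question on reaction to allocation or ask leavers for their reasons. That limits how firmly the second point can be put. It does not touch the first, because the timing of the satisfaction rating is stated outright. Women may also miss a late in-person class for obstetric reasons unrelated to satisfaction, which is why the upward direction is likely rather than certain.

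**Conclusion.** Two limited points hold.

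First, the satisfaction result will come from a selected group, those present at session 9, and is likely too favourable as a description of everyone allocated to MBSR. The size depends entirely on attendance and on absentees' opinions, neither of which the article gives. Under the assumed rates, the gap between the reported and the whole-arm value at 40% satisfaction among absentees runs from about 5 percentage points (89% against 84%, 27 attending) to about 27 (93% against 67%, 15 attending). The other acceptability components are unaffected.

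Second, the stated purpose on resentful demoralization is not matched by any described measure of reaction to allocation. It rests on signals that cannot separate demoralization from other causes and that, at about 30 per arm, carry half-widths of roughly 15 to 23 percentage points for a difference in dropout.

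Neither point undermines the recruitment, compliance or retention results. Both are worth correcting because these findings are meant to shape the full trial.

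**What to change.** 1. Put the satisfaction items in the existing REDCap questionnaire sent immediately after the program, and send it to every woman allocated to MBSR, including those who stopped. Report the result over all allocated, with non-responders shown as their own category.
2. Add one or two items on reaction to the allocation to the same questionnaire in both arms, and state that they serve the purpose named under Blinding.
3. Use one list of acceptability components in the primary outcome and Data analyses sections, and say whether satisfaction belongs to it.

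The online system and its one-week email reminder are already in place, so the change is small. The cost is slightly more respondent burden. Some women who stopped will not reply, so the selection is reduced and made visible rather than removed.
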